## Abstract

**Introduction:**

Unilateral aldosterone-producing adenomas (>1 cm) and aldosterone-producing nodules (<1 cm) are a common cause of primary aldosteronism (PA) and hypertension. Adrenal surgery can potentially cure or significantly improve the condition. However, fewer than 1% of patients with PA undergo adrenalectomy. For some, this is due to surgical risks, service capacity or patient preference against surgery. In these individuals, thermal ablation may provide an alternative. This paper describes the protocol for the WAVE trial, designed to compare thermal ablation with the current standard, laparoscopic adrenalectomy, in the treatment of unilateral PA.

**Methods and analysis:**

WAVE is a prospective, multicentre, randomised controlled non-inferiority trial comparing thermal ablation (experimental arm) with laparoscopic adrenalectomy (control arm) in the treatment of unilateral PA. 122 participants will be recruited and randomised to thermal ablation or laparoscopic adrenalectomy in a 1.5:1 ratio. Hierarchical co-primary endpoint data considering both biochemical and clinical outcomes will be judged at 6 months. Secondary endpoint data will consider adverse events, length of inpatient stay, patient satisfaction and time to return to activities of daily living. The full protocol is available at ClinicalTrials.gov.

**Ethics and dissemination:**

The protocol was approved by the Bloomsbury Research Ethics Committee (21/LO/0243). The results of the study will be shared with study participants, published in peer-reviewed journals and presented at national/international conferences.

**Trial registration number:**

NCT05405101.

STRENGTHS AND LIMITATIONS OF THIS STUDYWAVE is a PROBE (Prospective Randomised Open-Label with Blind Endpoint determination) trial that uses international consensus criteria to determine biochemical and clinical outcomes.The analysis will report the outcomes of both left-sided (endoscopic) and right-sided (percutaneous) thermal ablation, using radiofrequency or microwave techniques.Molecular positron emission tomography imaging is being used pre-ablation and post-ablation to evaluate the extent of ablation of the targeted nodule(s).Immunohistochemical and/or molecular (RNA sequencing/quantitative PCR) confirmation of correct targeting of the ablated nodule is possible for left-sided ablations, but not routinely for those on the right.WAVE evaluates emerging interventional strategies designed to expand the availability of non-surgical modalities for the management of primary aldosteronism.

## Introduction

 Primary aldosteronism (PA) is the most common cause of secondary hypertension. It is responsible for 5–10% of all hypertension^1 2^ and up to 20–25% of resistant cases.^2^ PA is a high-risk subset of hypertension associated with a twofold higher rate of cardiovascular events and atrial fibrillation relative to age-matched and gender-matched patients with essential hypertension.^3 4^ It is also linked to reduced quality of life.^5^

Aldosterone excess in PA may originate from one or both adrenal glands. Unilateral PA is usually caused by an aldosterone-producing adenoma (APA)/aldosterone-producing nodule (APN) and is conventionally treated with surgical removal of the culprit adrenal gland. While medical therapies such as mineralocorticoid receptor antagonists (MRAs) address aldosterone excess, surgery may be more effective in reducing cardiovascular^6^ and stroke^7^ risk, and improving quality of life.^8^ Furthermore, sufficient MRA dosing to de-suppress renin and mitigate this excess risk is only achieved in one-third of medically treated patients.^3^

Surgery for PA conventionally involves removal of the whole adrenal gland to treat a condition caused by a small (usually <2 cm diameter, and often <1 cm) benign APA/APN. A return to full physical activities takes several weeks and the clinical outcome is uncertain, with only a minority of people stopping anti-hypertensive medication altogether. An alternative intervention to laparoscopic adrenalectomy, and the focus of this trial, is selective thermal ablation (by radiofrequency or microwave) of the identified APA/APN(s). Thermal ablation is a technique in which targeted and directed tissue death can be achieved with precision under image guidance, sparing the normal adrenal gland.

The primary objective of WAVE is to test the hypothesis that thermal ablation (using either microwave or radiofrequency (RFA)) is non-inferior to surgery in the biochemical (and if so, in the clinical) cure of unilateral PA, according to the international consensus primary aldosteronism surgical outcomes (PASO) criteria.^9^

## Methods

This study received ethical approval by the London—Bloomsbury Research Ethics Committee (21/LO/0243, [contact]). The trial registration number is NCT05405101.

### Trial design

WAVE is a prospective, multicentre, randomised controlled non-inferiority trial comparing thermal ablation (experimental arm) with laparoscopic adrenalectomy (control arm; current standard of care) in the treatment of unilateral PA. Adult patients with unilateral PA (proven by adrenal vein sampling and/or molecular imaging) who are candidates for unilateral adrenalectomy, but in whom thermal ablation is also technically feasible, will be recruited. Participants will be randomised in a 1.5:1 fashion to either ablation or surgery. The trial started recruiting in September 2022 and is anticipated to complete recruitment in early 2026. Allowing for 6 months following intervention until collection of primary endpoint data, the trial is expected to complete in mid 2027.

The primary hypothesis of WAVE is that thermal ablation is non-inferior to surgery in the treatment of unilateral PA due to an APA/APN. WAVE is an ‘inferiority non-inferiority study’ design^10^ and draws on experience from other areas of medicine, in which numerically ‘worse’ treatments in terms of efficacy may be deemed ‘non-inferior’ by virtue of other advantages, such as procedural safety, drug toxicity and overall patient acceptability. This approach in clinical trials design requires careful consideration of an appropriate, prespecified non-inferiority margin. This, in turn, is influenced by the severity of the endpoint, the availability of other options in the event of treatment failure and the anticipated benefits of the experimental intervention if adopted into routine clinical practice. Non-inferiority margins in this context are determined by a combination of patients’ views and the opinions of experienced clinicians/investigators in the field. Selected APA thermal ablation cannot be superior to surgical removal of the whole adrenal (which may also harbour additional microscopic foci of autonomous aldosterone production), but is balanced against its less invasive nature. The public and patient involvement in the setting of the non-inferiority margins for WAVE is described in detail in the relevant section.

### Setting

The trial is coordinated at Queen Mary, University of London and involves six participating centres:

Barts Health NHS Trust,University College London Hospital NHS Foundation Trust,Imperial College Healthcare NHS Trust,Cambridge University Hospitals NHS Foundation Trust,Guy’s and St Thomas’ NHS Foundation Trust andSheffield Teaching Hospitals NHS Foundation Trust.

Left-sided ablations will be performed at sites 1, 2 and 4. Right-sided ablations will be performed at sites 1, 3 and 4. Unilateral adrenalectomy may be performed at all sites.

### Study inclusion

122 adults with unilateral PA will be recruited to WAVE. The full inclusion and exclusion criteria are listed in box 1.

Box 1. Inclusion and exclusion criteria
Inclusion criteria
Participants must meet all of the following:Age >18 years.Primary aldosteronism according to international guidelines.^15 16^An elevated aldosterone renin ratio (according to local reference ranges), and at least one of (when measured off confounding medications):Spontaneous or diuretic-induced hypokalaemia, plasma aldosterone concentration >550 pmol/L and plasma renin activity (PRA) <0.5 nmol/L/hour or direct renin concentration (DRC) <4.2 mU/L.A positive saline infusion test.4-hour aldosterone >190 pmol/L on immunoassay (or equivalent, >160 pmol/L on mass spectrometry).A positive captopril challenge test, either:Failure to suppress 2-hour aldosterone by >30% and persistent suppression of PRA/DRC^15^, or2-hour aldosterone >300 pmol/L^16^ (by immunoassay or equivalent on alternative assay).Unilateral primary aldosteronism (PA), defined by at least one of the following criteria:Adrenocorticotropic hormone (ACTH)-stimulated adrenal vein sampling (AVS).^17^Selectivity Index (SI) >3, andLateralisation Index (LI) >4.Non-ACTH-stimulated AVS.^17^SI >2, andLI >3, andContralateral Suppression Index <0.5.Metomidate/para-chloro-2-[^18^F]fluoroethyletomidate (CETO) positron emission tomography (PET)-CT.^18 19^>25% higher PET signal (maximum standardised uptake value) over a focal adrenal macro (>1 cm) or micro (<1 cm) nodule compared with the contralateral adrenal.Age <35, marked PA, unilateral focal adrenal lesion with normal contralateral gland.^15^Radiological abnormality ipsilateral to side of lateralisation, which is:Benign:Unenhanced CT attenuation <10 Hounsfield units, orPost-contrast CT absolute washout >60%, orPost-contrast CT relative washout >40%, orSignal drop-out on out-of-phase MRI.Technically amenable to both ablation and surgery (determined at multidisciplinary team (MDT) review). This excluded participants with morbid obesity.Able and willing to give informed consent.Randomisation approved by MDT.
**Exclusion criteria**
Potential participants will be ineligible to enter the study if they meet any of the following exclusion criteria:Absolute contraindication to α-adrenoceptor or β-adrenoceptor antagonist therapy or CT contrast, orContraindication or unwillingness to undergo either surgery or ablation, orInability to withdraw β-adrenoceptor antagonist therapy for 2 weeks, orUnwilling to comply with study visit schedule, orPregnancy or unwillingness to undertake secure contraception for the study duration (female participants only), orLife-limiting comorbidity (at the discretion of the principal investigator), orClinical and/or biochemical evidence of autonomous cortisol secretion sufficient, in the opinion of the patient’s physician, to mandate a unilateral adrenalectomy independent of autonomous aldosterone secretion, orAldosterone-producing adenoma diameter >2.5 cm.

### Study procedures

The timeline for the study is shown in figure 1.

**Figure 1 F1:**
[figure not shown]
Study timeline following screening, participants are discussed at the MDT and, if deemed suitable, invited for enrolment and randomisation. They will then embark on the surgical or thermal ablation pathway. Patients undergoing thermal ablation require a Metomidate/CETO PET-CT as well as a period of pretreatment with α-adrenoceptor and β-adrenoceptor antagonists prior to intervention. Primary endpoint data are collected at 6 months but patients who reach that end point before the end of the trial will also be seen at 12, 24 and 36 months post-intervention. *Some patients will require two thermal ablations, **the post-ablation PET-CT will occur 3–6 months after the procedure. CETO, fluorine-18-labelled para-chloro-2-fluoroethyl-etomidate; MDT, multidisciplinary team; PET, positron emission tomography.

#### Recruitment/screening

Patients with confirmed unilateral PA who express an interest in participating will be identified for recruitment and given a participant information sheet (PIS). Contact details for the trial coordinator are published online to provide an opportunity for patients cared for at other centres to enquire about potential trial participation.

#### Multidisciplinary team meeting

All potential participants will be discussed at the multidisciplinary team (MDT) meeting and eligibility criteria will be scrutinised and recorded. The MDT comprises representatives from all centres and includes clinicians and investigators with the necessary expertise to inform each of the following eligibility criteria:

Confirm diagnosis of unilateral PA (endocrinologist/hypertension specialist).Confirm benign adrenal lesion (radiologist).Confirm surgical candidacy (endocrine surgeon).Confirm candidacy for percutaneous CT-guided thermal ablation (interventional radiologist).Confirm candidacy for endoscopic ultrasound (EUS)-guided RFA (interventional endoscopist).

In patients who have unilateral disease on adrenal vein sampling (AVS) and/or positron emission tomography (PET)-CT, the MDT may exercise discretion to include patients who have not met every component of the Endocrine Society’s consensus guidelines for the diagnosis of PA but where the diagnosis is universally accepted by all principal investigators (PIs). For example, a patient with hypokalaemia with a fully suppressed renin (in the absence of a beta-blocker) but where aldosterone does not quite achieve 550 pmol/L and a confirmatory test has not been performed would be eligible for inclusion.

#### Enrolment visit and randomisation

Following confirmation of eligibility by the MDT, participants will attend for enrolment. Informed written consent will be obtained by a Good Clinical Practice-trained member of the clinical research team. The consent form can be found in online supplemental material 1. No incentives were provided to participants for taking part in the study. Baseline clinical data, blood and urine samples will be collected and 24 hours ambulatory blood pressure monitoring (24hABPM) will be performed. Quality of life (EuroQol 5-Dimension 5-Level questionnaire (EQ-5D-5L), 36-Item Short Form Health Survey (SF-36)) questionnaires will be completed.

Patients will be randomised using a minimisation technique in a 1.5:1 ratio to ablation or surgery, stratified according to site, laterality (left vs right), gender (male vs female) and ethnicity (non-black vs black) by a computerised system operated by King’s College London Clinical Trial Unit (KCTU). Due to the nature of the interventions, blinding or sham procedures are not appropriate.

If randomised to thermal ablation, patients whose PA was lateralised by AVS will undergo molecular adrenal imaging in order to localise the ablation target. All patients recruited from Site 1 will be invited to have a non-compulsory cardiovascular magnetic resonance scan (CMR).

#### 2-week pre-ablation visit (thermal ablation group only)

For patients undergoing thermal ablation, α-adrenoceptor and β-adrenoceptor antagonists will be initiated, and subsequently titrated, 2 weeks prior. This is to mitigate the risk of a procedural hypertensive emergency due to adrenomedullary stimulation. The exact choice of agent will be at the discretion of the site PI, with suggested starting doses of doxazosin 2 mg two times a day and bisoprolol 2.5 mg once daily. After 1 week, these will be up-titrated aiming for a dose of doxazosin of 4 mg two times a day and bisoprolol 5 mg once daily if tolerated. Depending on blood pressure (BP) control, additional alteration of concomitant anti-hypertensive therapy may be required, with the choice at the discretion of the PI.

#### Ablation

Thermal ablation will be delivered using CT-guidance for right-sided APAs and EUS-guidance for left-sided APAs. Procedures may be performed under general anaesthetic or sedation with BP monitoring, invasive or non-invasive, at the discretion of the supervising anaesthetist.

Prior to thermal ablation, if feasible, research fine needle biopsies of the APA and adjacent normal adrenal tissue will be taken for immunohistochemistry, gene expression and somatic mutation analysis. RFA is performed using a 5 or 10 mm 19G STARMed (Gyeonggi-go, Korea) ablation catheter. The stomach is able to self-seal following ablation. For right-sided APAs, the intention is to ablate from a retroperitoneal approach avoiding lung, kidney and liver. However, in selected cases, a transhepatic approach may be used where required in order to avoid the lung and the risk of pneumothorax.

During the ablation, the following details will be recorded: duration of procedure, medications administered, maximum BP as well as the number and duration of treatments (‘burns’). Plasma metanephrines will be taken three times on the day of the thermal ablation procedure (pre-anaesthetic, post-anaesthetic/sedation but prior to insertion of the ablation catheter and during ablation). Additional samples for plasma metanephrines will be collected if there is a clinically concerning rise in BP and/or heart rate during or immediately after the procedure.

A specific potential risk of APA thermal ablation (which is not shared in laparoscopic adrenalectomy) is stimulation of catecholamine release from the adjacent adrenal medulla which can result in significant hypertension and tachycardia akin to a ‘phaeochromocytoma crisis’. In order to mitigate against this risk in WAVE, patients will be alpha and beta blocked pre-ablation and have BP monitoring during the procedure with necessary pharmacological agents at hand if required. Standard safety considerations apply to the risk of bleeding and pneumothorax.

Following thermal ablation, participants will be monitored according to local protocol and can be discharged on the same day. The following day, participants will return for a clinical review and protocol-specified blood tests. Antihypertensive medications will be optimised accordingly with a preference for classes that do not significantly interfere with measurements of renin and aldosterone.

#### Surgery

Laparoscopic adrenalectomy will, in general, be carried out at the enrolling site, according to local standard operating procedure (SOP), but may, if the patient wishes, be carried out at the referring centre. Alternatively, should the patient or local PI feel it is more appropriate, then it may be carried out elsewhere.

During surgery, the following details will be recorded: duration of procedure, medications administered and maximum BP. Plasma metanephrines will be taken three times on the day of surgery (pre-anaesthetic, post-anaesthetic but pre-procedure and during the surgery). Both APA and adjacent normal adrenal tissue will be collected for immunohistochemical analysis, gene expression and somatic mutation analysis.

On postoperative day 1, participants will be seen for a clinical review and protocol-specified blood tests. Antihypertensive medications (if required, with a preference for those that do not interfere with measurements of renin and aldosterone) will be optimised.

#### Second ablation

A small subset of patients will be offered a second ablation following MDT discussion. This would not usually be considered if the nodule is <2 cm in maximum diameter. For patients with more than one left-sided adrenal nodule, if the repeat PET-CT shows that thermal ablation did not target the likely APA and instead another adrenal nodule was ablated, a second ablation procedure will be recommended.

#### Post-intervention visits at 6 weeks and 3, 6, 12, 24 and 36 months

Clinic and home BP measurements will be recorded at each visit. Medication history will be reviewed, and antihypertensive medication titrated according to BP.

Secondary outcome data, including patient satisfaction and date of return to usual activities of daily living, will be completed at 6 weeks.

Patients in the thermal ablation group will have a post-ablation Metomidate or CETO PET-CT scan at 3 months to help assess whether there is any residual APA following ablation. Patients can be offered a second ablation if the criteria described previously apply.

Primary outcome data will be collected at the 6-month visit. All interfering medications that could affect aldosterone or renin will be stopped prior to the appointment. If the aldosterone renin ratio (ARR) is elevated, a confirmatory test (saline infusion test or captopril challenge test at the local PI’s discretion) will be performed. 24hABPM and quality of life questionnaires (EQ-5D 5L, SF-36) will be collected at this visit. For patients who had a CMR at enrolment, the scan will be repeated.

While the trial is ongoing, patients who reach the 12-month, 24-month and 36-month mark post-intervention will be scheduled for a study visit.

#### Adrenalectomy post-ablation

Participants who undergo thermal ablation and do not experience complete biochemical success by PASO criteria at the 6-month time point may be offered a unilateral adrenalectomy as standard treatment for lateralised PA. This will only be considered after MDT review of the post-ablation PET-CT. If surgery occurs during the course of the trial, 6-month post-surgical follow-up will be recorded as for other surgical patients but will not constitute the primary outcome data.

#### End of study visit

The end of the study is defined as the final study visit of the final participant. This will be the 6-month post-intervention visit of the final participant.

### Ablation therapy

Participants randomised to thermal ablation will undergo assessment by the treating clinician (endoscopist for left-sided APA, interventional radiologists for right-sided APA). RFA will be used for left-sided APAs, guided by endoscopic ultrasound. For right-sided APAs, microwave or RFA will be selected at the discretion of the interventional radiologist, based on location of the APA and their expert opinion on which method is most likely to be effective.

### Outcomes

WAVE is a PROBE (Prospective Randomised Open-Label with Blind Endpoint determination) trial. Both primary endpoints (biochemical indices and electronic BP monitor downloads) will be entered onto the electronic case report form (eCRF) by personnel blinded to the intervention.

#### Primary endpoint

Hierarchical primary endpoints will be adjudged at 6 months post intervention (for patients who have had two ablations, this will be 6 months post second intervention) and compared with the enrolment data:

Complete biochemical cure of PA, defined (while off medications that might alter serum potassium, renin or aldosterone) by both:Normalisation of serum potassium, andNormalisation of ARR, orElevated ARR andBaseline plasma aldosterone concentration <190 pmol/L on immunoassay (<160 pmol/L on mass spectrometry), orNormal confirmatory test (as defined in the inclusion criteria).Complete clinical cure of PA, defined as normotension without antihypertensive medication.

These criteria have been defined in the international consensus PASO statement,^9^ which has become the established yardstick by which outcomes following unilateral adrenalectomy are judged. In this, normotension is defined, in accordance with the European Society of Hypertension guidelines,^11^ as <140/90 in the office, <135/85 at home or daytime ambulatory monitoring and <130/80 for 24hABPM. The preferred method of assessment of BP will be via 24hABPM, with home BP allowable for subjects unable to perform 24hABPM.

In addition to the primary endpoint data, other exploratory analyses will include predictors of clinical success such as age, duration of hypertension and the dose and number of antihypertensives, in line with other published series.

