#### Secondary endpoints

Frequency and severity of adverse events will be reported throughout the study period and be classified by system, seriousness, causal relationship and expectedness according to the Common Terminology Criteria for Adverse Events V.5.0. Prespecified post-intervention safety aspects will be systematically evaluated and, where appropriate, compared between the two interventions, specifically anaemia, renal dysfunction and electrolyte abnormalities, liver dysfunction, pancreatitis and procedure-related hypertensive emergencies.

Length of inpatient stay will be recorded at the 6-week visit alongside patient satisfaction (Freiburg Index of patient satisfaction^12^) and duration to return to activities of daily living.

The anatomical efficacy of ablation will be assessed in the ablation group using molecular adrenal imaging appearances 3–6 months post ablation.

The presence of partial biochemical and clinical cure, as determined by the international consensus PASO statement,^9^ will be assessed as a secondary endpoint, while complete cure is a primary endpoint.

Post-intervention analysis of tissue samples will include histological grading according to the HISTALDO consensus^13^ (surgical specimens only), immunohistochemistry, studies of gene expression and genotyping for somatic mutations.

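### For twice-ablated participants the primary endpoint follows the second ablation, but stay, satisfaction and return to activities are recorded at 6 weeks, before it

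*Protocol article*

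**What the plan says.** **Second procedure.** The Second ablation section states: "A small subset of patients will be offered a second ablation following MDT discussion". It gives one specific trigger, for patients with more than one left-sided nodule: a second procedure is recommended "if the repeat PET-CT shows that thermal ablation did not target the likely APA and instead another adrenal nodule was ablated". No repeat procedure within the primary endpoint is described for surgery.

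**PET-CT timing.** Under Post-intervention visits, ablation patients "will have a post-ablation Metomidate or CETO PET-CT scan at 3 months to help assess whether there is any residual APA following ablation", and the possibility of a second ablation is mentioned directly after this. The Figure 1 caption says instead that "the post-ablation PET-CT will occur 3–6 months after the procedure", and Secondary endpoints also uses 3–6 months.

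**Primary endpoint.** It is judged at 6 months post intervention; "for patients who have had two ablations, this will be 6 months post second intervention".

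**Burden outcomes.** Under Secondary endpoints: "Length of inpatient stay will be recorded at the 6-week visit alongside patient satisfaction", together with time to return to daily activities. Under Post-intervention visits: "Secondary outcome data, including patient satisfaction and date of return to usual activities of daily living, will be completed at 6 weeks". Neither place has a provision for a second ablation.

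**Other outcomes.** "Frequency and severity of adverse events will be reported throughout the study period". EQ-5D-5L and SF-36 are collected at the 6-month visit, where the primary outcome is also taken. Under Adrenalectomy post-ablation, results of later surgery are kept out of the primary outcome data.

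**The concern.** The design trades efficacy against burden. Trial design says a numerically worse treatment may be accepted for its other advantages, and Sample size calculation uses the low morbidity of ablation to support the wide margin. Both sides of that trade should describe the same course of treatment.

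As printed they do not. The primary endpoint was re-anchored for twice-ablated participants and the three 6-week outcomes were not. A participant with two procedures would contribute cure after both, but stay, recovery time and satisfaction after the first alone. The mismatch can occur in the ablation arm only, and it makes ablation look lighter than the strategy that earned the cure rate. Statistical analysis says secondary hypotheses are tested with a focus on superiority, so the omission leans towards the result being sought. A later analysis cannot recover data that were not collected after the second procedure.

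**Working it through.** **1. Timeline of a twice-ablated participant, from the stated visits**

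| Event | Time from first ablation |
|---|---|
| Stay, satisfaction and return to activities recorded | 6 weeks |
| PET-CT that can lead to a second ablation | 3 months (or 3–6 months) |
| Second ablation | not before the PET-CT: at least about 3 months, or 6 if the scan is at 6 |
| Primary endpoint | second ablation + 6 months: at least 3 + 6 = 9 months, or 6 + 6 = 12 |

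Six weeks precedes every permitted scan time, so the three outcomes cover the first procedure only. A surgical participant has one procedure, with stay and recovery recorded at 6 weeks and the endpoint at 6 months, so no mismatch arises there.

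**2. The plan's own figure.** For limb 2, Sample size calculation assumes 90% v 65% cure, a 45-point margin, and 44 surgery and 66 ablation participants. With unpooled variance and one-sided 5%:

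SE = √(0.90×0.10/44 + 0.65×0.35/66) = √0.005492 = 0.0741

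Power = Φ((0.45 − 0.25)/0.0741 − 1.645) = Φ(1.054) = 0.854, against the stated 85%. The figure reproduces. The timing point does not depend on it.

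**3. What second ablations can add to cure.** The plan gives no number, so 3 or 5 of 66 is an assumption, with all of them cured and otherwise failures:

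- 3/66 = 4.5 points
- 5/66 = 7.6 points

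More generally, gain = (fraction re-ablated) × (fraction of those cured). Assuming 5–10% re-ablated and 50–90% of them cured, the gain runs from 0.05×0.50 = 2.5 points to 0.10×0.90 = 9 points.

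**4. What is left out of the burden outcomes.** If a fraction f is re-ablated and each second procedure costs d days, the arm's mean is understated by f×d. With f = 3/66 or 5/66, each such day adds 0.045 or 0.076 days to the mean. If a second recovery lasted as long as the average first one, mean total recovery would be 4.5% or 7.6% higher than recorded.

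**5. Effect on the limb 2 test.** Suppose single-ablation cure were exactly at the margin (45% v 90%), where the chance of a positive limb 2 is 5%.

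- 3 rescued: cure 49.5%, SE 0.0764, Φ(0.0455/0.0764 − 1.645) = 0.147
- 5 rescued: cure 52.6%, SE 0.0763, Φ(0.0758/0.0763 − 1.645) = 0.257

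These are the probabilities of a positive result when the up-to-two-ablation strategy truly has a higher cure rate. They take limb 2 alone and ignore that it is tested only if limb 1 succeeds.

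**The case against.** The strongest reply is that an up-to-two-ablation strategy is prespecified and openly stated, that the patient focus group raised a second ablation as a key theme, and that removal of the whole gland has no counterpart to it. That stands: the second ablation is not the flaw.

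It also stands that most burden is captured. Adverse events, including procedure-related hypertensive emergencies, run through the whole study, and quality of life is taken at the primary-outcome visit. None of the three outcomes in question enters the hierarchical test, so the mismatch cannot change the non-inferiority result. A reader might infer that burden after a second ablation goes unrecorded altogether; the text does not support that.

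A reader might also infer that known failures get another attempt and that a failed endpoint is then overwritten. The mis-targeting trigger is an imaging finding in patients with several left nodules, the general route is MDT discussion, and neither uses the biochemical endpoint. No section describes a second ablation after an adjudged failure. The 3–6 month wording only leaves this possible, because a scan at 6 months could coincide with the endpoint visit.

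Finally, the article is condensed and Figure 1 is not available here. The full protocol may restart the visit series after a second intervention. If so, the collection gap closes, and the article needs only to say so and say how the results are combined.

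**Conclusion.** The point holds as a mismatch of windows for three secondary outcomes. As printed, stay, satisfaction and return to activities exclude the second ablation, whereas the primary endpoint includes it, and this can happen in one arm only.

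The size is probably modest. If 3 or 5 of 66 are re-ablated and cured, cure gains 4.5 or 7.6 points. If a second recovery is as long as the first, mean recovery is understated by 4.5% or 7.6%. Both rest on assumed counts, since the plan speaks only of a small subset.

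The rise from 5% to about 15% or 26% shown above might be read as type 1 error inflation. It is not: the test remains valid for the strategy as defined, the figures place single-ablation cure exactly at the margin when planning assumes 65–70%, and they ignore the limb 1 gate. They show only that a positive result speaks for up to two ablations and not for one.

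This is an inexpensive improvement worth making, because these outcomes are among the advantages weighed against a wide margin.

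**What to change.** 1. Record length of stay, days to usual activities and satisfaction after every study procedure up to the primary endpoint, in both arms. Analyse total stay and total recovery days per participant, and report satisfaction after the last procedure.
2. State that a primary endpoint already adjudged at 6 months after the first ablation is not replaced by a later one.
3. Reconcile the PET-CT timing between Post-intervention visits (3 months) and the Figure 1 caption and Secondary endpoints (3–6 months).
4. As a supporting analysis, report limbs 1–3 with re-ablated participants counted as not cured. Label it a conservative bound on the single-ablation effect, because some of them might have met the endpoint without the second procedure.

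The cost is a few repeat questionnaires in a small number of participants, one extra analysis and some wording. Sample size and treatment rules are unchanged. Ablation results may look slightly less favourable.
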